**WP 1b**							
	Semistructured observations (n=3-5 clinic days)	HCPs^e^, clients, and staff at the health center		Client-provider interaction (n=10) Clinic processes Medical examination Medication procurement and delivery Locations of medication supplies, output, or storage		To understand current workflows regarding NCD management and care	
	IDIs (n=10-20)	Academics, implementers working on CVDs^f^ or mHealth^g^ interventions, and policy makers		Development and implementation of mHealth interventions Research on NCD management Current health care services		To develop a theory of intervention for implementation and scale-up	

^a^IDI: in-depth interview.

^b^NCD: noncommunicable disease.

^c^FGD: focus group discussion.

^d^CHW: community health worker.

^e^HCP: health care provider.

^f^CVD: cardiovascular disease.

^g^mHealth: mobile health.

#### Prototype: WP 2

WP 2 (Table 2) aims at finalizing the design prototype and preparing for pilot testing. To collect detailed feedback from end users and ensure that the final product aligns with their expectations, we will present a first MoPuleesa prototype on mobile devices to the end users. Luganda-speaking research team members on site will conduct think-aloud exercises, which will allow a much more targeted refinement of the prototype to address emerging barriers or challenges [42]. Think-aloud exercises are used to track a participant’s thoughts while using a platform and to capture their problem-solving process [43]. After a short practice phase, participants are asked to comment on each step they take while using the platform and to say out loud what thoughts come to mind [42]. To minimize potential biases, data collectors will be asked to not interrupt the exercise and not interact with participants during the exercise unless they stop speaking (whereupon participants will be encouraged to continue speaking). Furthermore, we will capture local policy makers’ and local leaders’ feedback on the prototype and envisioned implementation processes via IDIs to further refine the prototype and identify potential difficulties and facilitators for rollout.

**Table 2 table2:** Methods used in work package 2: think-aloud exercises and in-depth interviews.

Activities	Participants	Themes	Purpose
Think-aloud exercises (n≤40)	Clients, HCPs^a^, CHWs^b^ (who have or have not used a version of the prototype before)	Interaction with latest prototyped platform Usability of platform features	To refine the prototype to address emerging barriers or challenges
IDIs^c^ (n≤20)	Key stakeholders (policy makers and local leaders)	Latest prototype version Benefits and barriers Implementation process	To incorporate further concerns and perspectives

^a^HCP: health care provider.

^b^CHW: community health worker.

^c^IDI: in-depth interview.

#### Test: WP 3

In WP 3 (Table 3), we will pilot-test the final prototype. For the qualitative component of this WP, we will conduct IDIs with clients who were particularly engaged in previous interviews or who suggest during trial administration that they would like to expand on their responses in more detail to get a full understanding of their perspectives on the design and implementation process. In addition, to provide guidance on best practice approaches to co-designing mHealth interventions with end users, we will conduct IDIs with key stakeholders involved in this process, including health center staff, software developers, and members of the study team.

Quantitatively, we will assess differences between the top-up and subscription contribution options, as well as the impact of the intervention on service use, user satisfaction, intervention uptake and funds contributed, and clients’ blood pressure readings, in a 2-arm between-participants parallel randomized controlled trial.

Participants will be randomized to 1 of the following 2 intervention arms (for the randomization plan, refer to the *Sample, Sampling, and Data Collection* subsection):

**Table 3 table3:** Methods used in work package 3: in-depth interviews and randomized controlled trial.

Exercise			Participants		Themes		Purpose
**Qualitative**							
	IDIs^a^ (n=5-7)	Clients (particularly engaged in previous interviews or suggested during survey administration that they would like to expand on their responses in more detail)		Expectations toward the prototype Perception of implementation process		To assess experiences with the finalized prototype	
	IDIs (n=10-15)	Key stakeholders involved in the implementation process (health center staff, software developers, and members of the study team)		Team communication Implementation process Problem-solving		To provide guidance on best practice approaches to co-designing mHealth^b^ interventions with end users	
**Quantitative**							
	Trial (sample size: 250-350 clients)	All clients who have given consent to participate in the trial and take up a money-saving model		Baseline and follow-up survey Kano questionnaire [44] Aggregation of clinic data		To gather information on trial participants	

^a^IDI: in-depth interview.

^b^mHealth: mobile health.

Arm 1: subscription-based model, where individuals will be given the opportunity to enroll in a medication-specific mobile money savings account where they can deposit money over the course of the month. If clients reach the minimum amount needed to purchase medications for the following visit, the money will be automatically debited from their savings account at the end of each month.

Arm 2: top-up payment model, where clients can actively make mobile money transfers to the health facility throughout the month for the purchase of medication in the subsequent month without the option to make marked contributions for several months in advance.

### Main Hypothesis

For the comparison between these 2 subscription approaches (specifically study objective 3), we draw on ongoing discourses in the literature regarding the chances and challenges of monetary contribution approaches for various purposes. Our considerations included findings regarding the differences between restrained commitment accounts and flexible liquid accounts that suggest greater willingness to save with less account flexibility in cases where clients self-report awareness of their own limited saving discipline [45]. In addition, several scholars have suggested that marked savings accounts, similar to our proposed subscription-based model where clients can save money to cover automatically deducted monthly medication costs, increase utility costs for the later repurposing of already made marked savings and thereby can increase overall savings made for the intended purpose [46,47]. Furthermore, Fisher and Anong [48] have found that long-term saving motives as well as low risk tolerance might add to regular savings. Transferred to the setting at hand, this suggests that marked savings combined with regular and automated contributions might be preferred to ensure sustainable contribution and treatment.

When testing the developed prototype, our main hypothesis therefore is that the subscription model, combining benefits from committed, semiliquid, and long-term savings possibilities, will lead to more clinic visits, more intervention take up, and greater funds contributed to the health facility for the purpose of purchasing essential medications. We argue that, thanks to the ability to save dedicated funds in small increments for the explicit purpose of accessing a guaranteed medication stock, individuals in the subscription arm will be more likely to contribute to, and pick up, antihypertensive medications than individuals in the top-up payment arm. We will test whether this will lead to monetary savings (eg, individuals receive their medications through the public facility at a lower total cost than when purchasing out of pocket from a private pharmacy) and improved health (eg, individuals will be more consistent with picking up their medication and thus have improved blood pressure). We will evaluate the effect of the subscription model compared with that of the top-up payment model based on the outcomes listed in Table 4.

**Table 4 table4:** Outcomes.

Category	Outcome	Measurement
Primary outcome	Number of NCD^a^ clinic visits as well as number of medication pickups	Health facility records
Implementation and medication outcomes	Percentage of people who take up funding models Total amount contributed to the clinic funds	Directly from MoPuleesa platform
Long-term health outcome	Systolic and diastolic blood pressure readings	Collected through CHWs^b^ and health facility records
User experience outcome	User satisfaction	Questions on user satisfaction in baseline and follow-up surveys

^a^NCD: noncommunicable disease.

^b^CHW: community health worker.

Participants will be asked to fill out a questionnaire at baseline and after 6 months that will address care-seeking behavior, the consistency of medication pickups, health-related money-saving routines, and the perceptions of care quality. At baseline, the questionnaire will also include sociodemographic characteristics. At 6 months, the questionnaire will further include questions about the feasibility and acceptability of the intervention, as well as a short series of platform attribute or Kano-style questions (the Kano model describes the relationship between product attributes and user satisfaction or disapproval to determine the relative importance of product features [44]). In addition, we will use data routinely collected at clinic level (demographic data, blood pressure readings, and height and weight measurements) and via the MoPuleesa prototype (money contributed and medication ordered) as detailed in Table 4.

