#### Sample Size Estimation

On the basis of the range of recruited participants, we estimate the following minimal detectable effects (Table 5). For these calculations, our primary outcome is the number of clinic visits for medication pickups. On the basis of the 6-month study duration, this can range from 0 to 5 visits (individuals are asked to come once a month), which we will analyze as a count variable using Poisson regression. We additionally set an α of 5% and a power of 80%, with a 2-tailed *t* test for all estimates, and show the minimal detectable effects across a range of possible control counts (the number of visits for pickups among the voluntary contribution group in a range from 1 to 5) and sample sizes (ranging between 200 and 350). The minimum detectable effect is expressed as a rate ratio and measures the percentage increase in mean visits for the subscription contribution (intervention 1) compared with those for the voluntary contribution (intervention 2) over the 6-month study period.

**Table 5 table5:** Minimum detectable effect size across sample sizes and base rates.

Mean number of visits in the voluntary contribution (intervention 2) group	Minimum detectable effect size			
	200^a^	250^a^	300^a^	350^a^
1	1.44	1.39	1.35	1.32
2	1.30	1.27	1.24	1.22
3	1.24	1.22	1.20	1.18
4	1.21	1.19	1.17	1.16
5	1.19	1.16	1.15	1.14

^a^Total sample size (50% intervention 1 and 50% intervention 2).

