#### Quantitative Data Analysis

We will summarize participant demographic characteristics and assess baseline balance between those randomized to the top-up and subscription arms. We will then assess the effect of offering the subscription model on the number of clinic visits with medication pickups (the main outcome) by comparing differences between those *offered* (including those who were offered and did not take up) the subscription model and those *offered* the top-up contribution model. As not all individuals will take up the offer, this will represent the intention-to-treat effect. We will estimate this effect using Poisson regression models. Next, we will assess the effect of the amount of money an individual contributed on the number of visits they attend. We will do this using a Poisson instrumental variable regression approach, where we use the random assignment as an instrument for the amount of money contributed. Finally, we will assess the effect of the random assignment to the different contribution arms on the proportion of individuals who take up the contribution model (the implementation outcome) using linear probability models and the effect on systolic and diastolic blood pressure readings using linear regression models.

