#### Statistical Analysis

The baseline characteristics of participants will be compared between the 2 arms using medians and IQRs for continuous variables and proportions for categorical variables. Outcomes will be analyzed by both the intention-to-treat and per-protocol analysis methods using mixed effects Poisson regression methods for the primary outcomes. We will adjust for baseline imbalances for both the primary and secondary analyses, and both unadjusted and adjusted analyses will be presented. All our regression models will additionally control for baseline patient characteristics such as age, sex, and income to increase the precision of the treatment effects. We will not only conduct a complete case analysis but also present the results using multiple imputation as sensitivity analyses. Missing data on outcomes and key covariates will be assessed before analyses. Where applicable (missingness >10%), we will implement multiple imputation methods appropriate for random effects models. Two-tailed *P* values of ≤.05 will be considered to indicate statistical significance. Analysis will be performed with Stata software (version 17; StataCorp LLC). We will not conduct any interim analysis for this study.

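### The primary outcome is two counts in Table 4 but one combined count in the sample-size and analysis sections, so the count that decides the trial at P≤.05 is not fixed

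*Protocol article*

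**What the plan says.** The protocol article describes the primary outcome in four places, and they do not agree.

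- **Table 4 (Main Hypothesis section), primary row:** "Number of NCD^a^ clinic visits as well as number of medication pickups", both taken from health facility records.
- **Sample Size Estimation:** "our primary outcome is the number of clinic visits for medication pickups". Over six months it runs from 0 to 5, and Table 5 is built on it at a two-sided alpha of 5% and 80% power.
- **Quantitative Data Analysis:** the effect is assessed on "the number of clinic visits with medication pickups (the main outcome").
- **Statistical Analysis:** "mixed effects Poisson regression methods for the primary outcomes", in the plural and without saying which. The significance threshold there is a two-tailed P of .05 or less.

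The Main Hypothesis text also predicts that subscription "will lead to more clinic visits, more intervention take up, and greater funds contributed to the health facility". It then says that effects will be evaluated on the outcomes in Table 4. That table places take-up and funds under "Implementation and medication outcomes", not in the primary row.

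**The concern.** Total clinic visits and visits with a medication pickup are different quantities. A client who attends and leaves without medicine adds one to the first and nothing to the second. Such visits are plausible here. The Introduction says that public availability of medicines for long-term conditions is generally low. Under the clinic's existing scheme, clients who did not contribute could draw only on government stock. The arms differ in how clients pay for medicine, and the Main Hypothesis section expects the subscription arm to be likelier to contribute and to collect. The chance of a pickup at a given visit may therefore differ by arm, and the two counts could point to different conclusions.

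Neither participants nor the research team are blinded once the programme starts (Blinding section). If the document supports more than one primary count, the one reported as decisive can be settled after results are visible.

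**Working it through.** **1. What Table 5 was sized for.** Inputs from Sample Size Estimation and Randomization: two-sided alpha 0.05, power 0.80, 1:1 allocation, total N of 200 to 350, comparison-arm mean m of 1 to 5 visits. For a two-sample Poisson comparison with n = N/2 per arm, solve for the rate ratio RR:

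ln(RR) = (1.960 + 0.842) × sqrt[(1/m + 1/(m × RR)) / n]

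For m = 1 and N = 200 (n = 100), try RR = 1.44: sqrt[(1 + 0.694)/100] = 0.130; 2.802 × 0.130 = 0.365; exp(0.365) = 1.44, the printed value.

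| Mean | Recomputed, N = 200/250/300/350 | Table 5 |
|---|---|---|
| 1 | 1.440/1.389/1.352/1.324 | 1.44/1.39/1.35/1.32 |
| 3 | 1.243/1.216/1.196/1.181 | 1.24/1.22/1.20/1.18 |
| 5 | 1.185/1.165/1.150/1.139 | 1.19/1.16/1.15/1.14 |

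All 20 cells agree to about 0.005. Table 5 is therefore the calculation for one count tested once at 5%.

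**2. What counts under each definition.**

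| Event | Table 4, visits | Table 4, pickups | Sample Size Estimation and Quantitative Data Analysis |
|---|---|---|---|
| Visit with pickup | yes | yes | yes |
| Visit without pickup | yes | no | no |

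If pickups happen only at visits, Table 4's second item is in effect the combined count, and the real addition is total visits.

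**3. Error rate under each reading.** Each test is two-sided at 0.05.

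- *The combined count alone decides:* 5%.
- *Both Table 4 counts must be significant:* at most 5%. With no effect on either count it is 0.25% if independent (0.05 × 0.05) and 2.2% at correlation 0.8.
- *Either Table 4 count suffices:* 1 − P(|Z1| < 1.96 and |Z2| < 1.96) for bivariate normal test statistics. Independence gives 1 − 0.95² = 9.75%.

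| Assumed correlation | 0 | 0.5 | 0.8 | 0.9 | 0.95 |
|---|---|---|---|---|---|
| At least one false positive | 9.75% | 9.1% | 7.8% | 7.0% | 6.5% |

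The document gives no correlation. Both counts come from the same clients and the same records, so the upper end of the range is the more realistic.

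**4. Cost of keeping two counts with success on either.** A Bonferroni split of 0.025 each replaces 1.960 by 2.241 in step 1. The detectable rate ratios at N = 200/250/300/350 become 1.49/1.43/1.39/1.36 at mean 1, 1.27/1.24/1.22/1.20 at mean 3 and 1.21/1.18/1.17/1.15 at mean 5.

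**The case against.** The best defence is that the operative outcome can be recovered. Two sections name one count, Table 5 is sized for one, and the row label in Table 4 is singular. The trial is a pilot whose sample was set by the available clients, and the Limitations section disclaims broad efficacy statements. A multiplicity rule could also sit in a plan that is not shown. Much of this stands, and it limits the claim. It does not remove the contradiction: the Main Hypothesis section refers the reader to Table 4 for the outcomes, so Table 4 cannot be set aside as shorthand, and an unseen rule would not reconcile definitions that conflict in print.

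Two stronger readings are tempting and should not be drawn.

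- *That the 5% error rate is breached.* This needs a rule that success on either count suffices. No section states one, and the wording in Table 4 could equally mean both.
- *That the main hypothesis sets up three primary endpoints.* Three independent tests would give 1 − 0.95³ = 14.3%, but Table 4 already ranks take-up and funds outside the primary row, and Quantitative Data Analysis calls take-up the implementation outcome. A broad hypothesis served by ranked outcomes is ordinary.

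It is also fair to say that the practical gap between the definitions is unknown, because the document does not say how often a visit ends without a pickup.

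**Conclusion.** The point holds as an inconsistency in the definition of the primary outcome. Table 4 has two counts, Sample Size Estimation and Quantitative Data Analysis have one, and Statistical Analysis has an unnamed plural. Following the document does not tell the analyst which result decides the trial.

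The consequence for the type I error rate is conditional: the 5% level is not secured, rather than shown to be exceeded. The plausible excess is about 1.5 to 3 percentage points (6.5% to 8%), and 4.75 points (9.75%) under independence. Either excess arises only if one significant count of the two would be accepted as success. These figures rest on assumed correlations; the contradiction in definitions rests on none.

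**What to change.** - In Table 4, give one primary outcome: *number of clinic visits with a medication pickup over the 6-month study period*. Move total NCD clinic visits to a secondary row.
- In Statistical Analysis, where the text reads "using mixed effects Poisson regression methods for the primary outcomes", change the last word to the singular.
- In Main Hypothesis, add that take-up and funds contributed are secondary (implementation) outcomes, as Table 4 already ranks them.

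Table 5 then stands unchanged, and both counts are still collected and reported. If the team prefers two primary counts, it must state whether one or both must succeed. If one suffices, it must split alpha and recompute Table 5 as in step 4 of the working.

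The cost is a wording amendment. Recruitment began in August 2023, and Ethical Considerations requires modifications to go to both ethics committees, the national council and the trial register. The amendment should be made before outcome data are examined by arm.

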### Participants and Inclusion Criteria

Across all WPs, the respondent groups include HCPs at facility and community levels (medical doctors and clinic staff), CHWs working in the community, community members and key stakeholders (religious and local leaders, members of pooled financing schemes, and academics), clients (diagnosed with hypertension and living within the catchment area of Semuto Health Center IV), and decision makers (policy makers and ministry of health representatives). In the final WP, we also include study team members involved in intervention design, implementation, and evaluation processes as respondents.

Ethnicity, race, political orientation, religion, and class are not criteria for inclusion or exclusion in this study. Respondents must be aged ≥18 years to participate. Persons who are incapacitated (mentally challenged or physical disability: hearing and speech impaired) are excluded from this study. Textbox 1 summarizes the inclusion and exclusion criteria for this study.

Study inclusion and exclusion criteria.
**Inclusion criteria (aged ≥18 y and having given informed consent)**
Health care providers: community health workers, medical doctors, clinic staff working at Semuto Health Center IV or in community outreach in Nakaseke district, etcLocal key stakeholders: religious and local leaders, members of financing schemes, academics, etcClients: clients who have been diagnosed with hypertension and are registered at Semuto Health Center IVDecision makers: policy makers, ministry of health representatives, health insurance representatives, district administrators, etcStudy team members: individuals involved in the intervention design, implementation, and evaluation
**Exclusion criteria**
Refusing or withdrawing informed consentNot responding to invitations to participatePersons who are incapacitated (mentally challenged or physical disability: hearing and speech impaired)

### Sample, Sampling, and Data Collection

#### Qualitative Components

For the qualitative components of this study, we expect to recruit a maximum of 160 individuals. In line with the tenets of saturation (new data cease to provide fundamentally novel insights) [49] and information power [50], our sample size will be determined as data are collected. The aforementioned estimate is based on experience and an effort to achieve a justifiable trade-off between collecting high-quality data and minimizing strain on the target populations (eg, individuals to be interviewed) [51].

We will use purposive sampling [52] for WP 1 and WP 2 to gain a range of perspectives. Local leaders, policy makers, and academics will be contacted and recruited through the official communication channels for the respective health facility or office or via the established channels of African Community Center for Social Sustainability (ACCESS) Uganda. Health care professionals will be contacted through the respective clinics or when conducting structured observations once the clinics have agreed to participate. We will use snowball sampling [53] as necessary to contact additional participants.

For clients, convenience sampling [52] will be used. Clients will be approached during structured observations in the clinic areas where they await NCD care (waiting time: minimum 30 min). As clinic days for NCD care are conducted once a week at the health facility, clients will additionally be purposively recruited via local HCPs guiding the study team toward a range of clients who represent different types of background characteristics using the sampling criteria: age group (those aged >50 y and those aged <50 y), gender (male and female), and condition (hypertension, diabetes, or both). The study will be briefly introduced using an information sheet. If clients signal interest to participate, contact information will be exchanged to schedule an IDI. All IDIs and FGDs will take approximately 60 minutes and will be conducted by researchers and research assistants, including CHWs who work in the area but not in the study setting. All research assistants will have gone through a 5-day training program in qualitative research and interviewing and will work together as teams of 2 people representing a moderator and a notetaker. Research assistants will be provided with interview guides that will be refined in group sessions during the 5-day training period and pilot-tested on 2 days with participants within the study setting.

